### Spanish-language adaptation

2.9.

All materials and activities (including concept and behavioral skills videos, videos featuring real patients and ICU physicians related to post-ICU coping for those in the intervention arm and educational materials in the control arm) were adapted into a Spanish-language version with the goal of being easily understandable and culturally relevant for Latin American Spanish speaking audiences. We also translated the workbooks, intervention website, and all patient-communication media (e.g., participant guides for the app, welcome postcards), which are delivered by Spanish bilingual CRCs or CRCs in conjunction with interpreters. The translation of content was performed in an iterative three-step process by a multidisciplinary team of native English- and Spanish-language speakers. The process involved an initial cultural and linguistic adaptation of key scripted content by an external group of community members and clinicians, creation of final versions of material by bilingual trial network members, and formal usability testing among bilingual participants. This adaptation process will be further enumerated in a future paper.

### Outcome measures

2.10.

Outcome data collection for randomized participants occurs at four timepoints as shown in Table 2: at randomization (i.e., baseline) as well as 1, 3, and 6 months post-randomization. The HADS total score at 1 month is the primary outcome of the trial. The HADS is a self-assessment questionnaire (range 0–42) assessing both anxiety (HADS Anxiety subscale) and depression (HADS Depression subscale) [50]. Additionally, the HADS is administered to both groups in the second half of each week of the 4-week intervention through the app during days 4 to 6, 11 to 13, 18 to 20 and 25 to 27. Scores from participants who complete the HADS after completing Week 4 are used as the Month 1 measure. Any participant who misses the Week 4 HADS measure are prompted to complete a month 1 HADS on day 30. Collection windows for Month 1 and Month 3 timepoints end the day before collection begins for the next timepoint and end two months after collection begins for the (final) 6-month timepoint.

Secondary outcomes include differences in the HADS total score at months 3 and 6, as well as the following measures completed at 1, 3, and 6 months: the HADS Anxiety and Depression subscales [50]; PTSS, used to assess ICU-related trauma (i.e., PTSD) by anchoring memory recall to hospitalization [51]; the Modified Patient Health Questionnaire-15 physical symptom scale (mPHQ-15), which is a ten-item version of the PHQ-15 measure of physical symptoms [52] previously adapted for post-ICU patients [53]; and the EQ-5D 100-point visual analog quality of life scale. See Supplementary Material Appendix B for detailed descriptions of outcomes.

### Data collection and management

2.11.

Clinical characteristics collected through medical chart review are entered by CRCs in electronic case report forms securely integrated within the REDCap data management system [54,55] and include: insurance status, highest level of care environment (ICU or stepdown unit) during hospitalization, component questions to derive Charleston Comorbidity Index [56], ICU primary admission diagnosis, highest level of respiratory failure support present during hospitalization, surgery during hospitalization, psychiatric and pain medications, illness severity (Acute Physiology And Chronic Health Evaluation II [APACHE II] component questions and score) [57], and length of hospital stay. All other data collected are entered by participants directly in the Blueprint app. In addition to outcome data, these measures include: date of birth (used to calculate age), address (used to derive area deprivation index [58]), marital status, sex, race, ethnicity, primary language, presence of instrumental support, presence of minor children in the home, work status the month before hospitalization, and highest grade completed in school. See Supplementary Material Appendix B for detailed descriptions of all study assessments.

The data coordinating center (DCC) at OHSU uses REDCap to merge study data collected directly with biweekly data transmitted securely from the app platform. Only DCC data managers can view all patient-level data and experimental conditions. Intervention arms are masked for statisticians until final analysis. DCC data managers actively monitor all data throughout the study, identifying records needing attention or correction (e.g., missing, outlier, discrepancy) by CRCs. The DCC sends a bimonthly recruitment and retention progress to study staff, which is discussed at regularly scheduled meetings.

### Statistical analysis

2.12.

Outcomes as well as patient characteristics will be characterized by group at baseline by mean (SD), median (IQR), and N (%), as appropriate. Analyses of primary and secondary outcomes will be performed utilizing constrained longitudinal data models (cLDA), which are mixed effects models where both groups are constrained to have the same baseline intercept. As recommended to improve precision [59,60], the model will be adjusted for randomization variables of site and primary language spoken. Random effects for subject and an unstructured covariance structure will account for correlation between repeated measures. Model estimates will include a shared baseline intercept, estimates for difference from baseline for 1–6 months, and estimates for difference between Blueprint and Education Control at 1–6 month timepoints. Estimates will be reported with a 95% CI and *p*-values will be used to determine significant differences.

In secondary subgroup analyses utilizing cLDA models as described above on subsets of participants, we will examine whether the intervention effects are consistent or vary in magnitude across pre-specified sociodemographic subgroups that might have comparatively less access to therapy on average: Black race, Hispanic ethnicity, and participants with Spanish as a primary language (i.e., participants using the Spanish-language version of the app). Sensitivity analyses will be performed to estimate how much loss to follow-up may have affected primary outcome effect estimates using cLDA models with 1-month values imputed from linear regressions of any available weekly HADS scores collected during the intervention.

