### Experimental condition allocation

2.5.

Within 48 h post-discharge, all enrolled participants are prompted by the mobile app to complete the HADS survey within the app. Patients with elevated HADS total scores (≥8) are stratified by language (English or Spanish) and auto-randomized within language group by the platform in a 1:1 group ratio using an adaptive, biased-coin minimization method to balance study site and the HADS total scale score < 20 vs. ≥20 in treatment group allocation [40]. This algorithm is programmed directly within the mobile app platform; details of the algorithm are in Appendix A of the Supplemental Material. After completing the baseline survey, the assigned Blueprint or Education Program content auto-populates the app platform and prompts program initiation.

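### The PTSS, mPHQ-15 and EQ-5D VAS models leave out the baseline HADS factor that allocation balances, so their standard errors may be slightly larger than needed

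*Protocol article*

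**What the plan says.** Section 2.5 (Experimental condition allocation) sets three allocation factors. Participants are "stratified by language (English or Spanish) and auto-randomized within language group", and biased-coin minimisation is then used "to balance study site and the HADS total scale score < 20 vs. ≥20 in treatment group allocation".

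Section 2.12 (Statistical analysis) applies one model family throughout: "Analyses of primary and secondary outcomes will be performed utilizing constrained longitudinal data models (cLDA", described as "mixed effects models where both groups are constrained to have the same baseline intercept". Its covariates come in one sentence, which gives better precision as the reason: "the model will be adjusted for randomization variables of site and primary language spoken".

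Section 2.10 (Outcome measures) lists PTSS, mPHQ-15 and EQ-5D VAS as secondary outcomes alongside the HADS measures. Nothing in the article brings baseline HADS into the models for those three.

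**The concern.** When allocation forces balance on a prognostic variable, the treatment estimate already benefits from that balance. A model without the variable still counts its variation as residual noise, so the reported standard error can exceed the true sampling variability. The usual remedy is to include every balancing factor. The article follows that reasoning for two of its three factors, citing precision, and omits the only one that measures severity of distress.

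A constrained longitudinal model carries each outcome's own baseline in the response vector. That settles the matter for HADS total and nearly settles it for the subscales. It does not settle it for PTSS, mPHQ-15 or EQ-5D VAS. At stake is some reported precision on outcomes that include PTSD symptoms and quality of life, both named in the aims (section 2.2).

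**Working it through.** **Inputs from the article.** The three allocation factors (2.5), the two model covariates (2.12), and 400 × (1 − 0.19) = 324 participants at 1 month, SD 8.7 and entry at HADS ≥8 (2.13, Table 1). The article gives no figure for the precision of these models. Its power statement for PTSS comes without an SD, so the effect cannot be expressed in scale units.

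**Assumed inputs.** Before truncation at HADS ≥8: correlation of own baseline with follow-up 0.4–0.6; HADS with own baseline 0.3–0.7; HADS with follow-up 0.2–0.5. HADS mean 18, which puts about 47% of those randomized at ≥20.

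**Step 1: width ratio.** Let b be the outcome's own baseline, y its follow-up and s the HADS stratum. The partial correlation of s with y given b is

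r = (r_sy − r_by·r_sb) / √[(1 − r_by²)(1 − r_sb²)]

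and the ratio of standard errors, with the stratum over without it, is √(1 − r²). Three cases, using correlations after truncation:

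- Assumed 0.5, 0.5, 0.3 gives r_by 0.476, r_sb 0.346, r_sy 0.201. Then r = 0.036/0.825 = 0.044 and the ratio is 0.999.
- Assumed 0.5, 0.5, 0.4 gives 0.463, 0.348, 0.273. Then r = 0.112/0.831 = 0.135 and the ratio is 0.991.
- Assumed 0.5, 0.3, 0.5 gives 0.475, 0.201, 0.345. Then r = 0.250/0.862 = 0.289 and the ratio is 0.957. With continuous HADS in place of the stratum, the same formula gives 0.934.

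Over the whole grid the ratio for the binary stratum runs from about 0.955 to 1.00. In 27 of the 36 combinations the reduction is under 2%.

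**Step 2: simulation.** 6,000 trials per scenario, n = 324, minimisation on site and HADS stratum within language. The coin probability of 0.8 is assumed. Analysis of covariance on own baseline stands in for the longitudinal model with complete data.

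| Assumed correlations (own baseline–follow-up, HADS–own baseline, HADS–follow-up) | Model SE without / with stratum | Ratio | True SD of estimate without / with | 95% CI coverage without / with |
|---|---|---|---|---|
| 0.5, 0.5, 0.3 | 0.0963 / 0.0962 | 0.999 | 0.0971 / 0.0972 | 0.948 / 0.948 |
| 0.5, 0.5, 0.4 | 0.0956 / 0.0948 | 0.991 | 0.0932 / 0.0931 | 0.956 / 0.955 |
| 0.4, 0.5, 0.4 | 0.1008 / 0.0995 | 0.986 | 0.1008 / 0.1007 | 0.952 / 0.949 |
| 0.4, 0.3, 0.5 | 0.0982 / 0.0941 | 0.958 | 0.0940 / 0.0937 | 0.960 / 0.951 |
| 0.6, 0.7, 0.5 | 0.0888 / 0.0884 | 0.996 | 0.0887 / 0.0885 | 0.954 / 0.955 |

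The true variability of the estimate hardly changes, because allocation has already balanced the stratum. What changes is whether the reported standard error reflects that. The Monte Carlo error of a coverage figure is √(0.95 × 0.05/6000) = 0.003, so only 0.960 stands clearly above nominal. None falls clearly below it.

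**Step 3: effect on power.** A comparison with 80% power under the planned model would have Φ[(1.960 + 0.842)/ratio − 1.960]. That is 81.6% at a ratio of 0.98 and 83.5% at 0.955.

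**The case against.** The strongest reply is that this hardly matters. Each outcome's own baseline absorbs most of what HADS could predict, the loss may be nil, and any error is conservative. The article gives no correlation from which to show a loss. One generic sentence covers all outcomes, and omitting a HADS stratum is sensible for the HADS models. Outcome-specific covariates and time interactions are also the kind of detail a condensed article leaves to the analysis plan.

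Most of this stands and limits the point to a refinement of three secondary analyses. It does not remove the point. The article does not leave the covariates open: it names them for every outcome, and the list departs from section 2.5 and from its own precision rationale.

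Three stronger readings are tempting and are not supported:

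- **A larger loss.** A reader might take a partial correlation of 0.2–0.3 and infer SE inflation of 1/√(1 − r²) = 1.021–1.048, equivalent to 324 × 0.04 = 13 to 324 × 0.09 = 29 participants. Those values describe continuous HADS, which minimisation does not balance. A median split keeps at most about 0.80 of a correlation under normality. On the same assumption r is then at most 0.16–0.24, inflation 1.013–1.030, and the equivalent loss 324 × 0.0256 = 8 to 324 × 0.0576 = 19.
- **An invalid test, or harm to the primary analysis.** Leaving out a balanced factor makes inference conservative here, and HADS total already carries its baseline.
- **A wrong language covariate.** Eligibility asks only for functional fluency in English or Spanish, so a reader might infer that primary language can differ from the stratum. Section 2.12 calls language a randomization variable and equates Spanish primary language with use of the Spanish app version. Nothing shows that the model would use a different value.

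**Conclusion.** The point holds as a minor one. The stated covariate list omits one of the three balancing factors, and for PTSS, mPHQ-15 and EQ-5D VAS nothing else in the model replaces it. Standard errors for those outcomes will be equal to or slightly larger than needed. Adding the binary stratum would reduce them by 0% to about 4.5%, mostly by under 2%, and continuous baseline HADS may recover somewhat more. These figures rest on the assumed correlations, HADS mean and coin probability, and on a complete-data approximation. The documents fix the omission and its direction, but not its size. If HADS adds nothing beyond an outcome's own baseline, the loss is zero. The treatment estimates are not biased, type I error is not inflated, HADS total loses nothing, and the subscales lose little.

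**What to change.** In the models for PTSS, mPHQ-15 and EQ-5D VAS, add baseline HADS total as a continuous covariate, or at least the <20/≥20 stratum. Include its interaction with time, so that its coefficient may differ between baseline and each follow-up visit. Leave the HADS total model as it is. If the sponsor prefers to omit the term, one sentence giving the reason would do.

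The cost is a change of wording in the analysis plan. Every randomized participant has a baseline HADS score, because randomization requires it. Recruitment is described as ongoing (section 2.4) and statisticians stay masked until the final analysis (section 2.11), so the term can still be prespecified. Added after unmasking, it could look data-driven.

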### Study objectives

2.2.

The aims of this study are to test the efficacy of Blueprint on improving symptoms of depression, anxiety, PTSD, and quality of life among cardiorespiratory failure survivors and to determine which patient-level characteristics are associated with a greater treatment response among sociodemographic subgroups of interest.

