### Sample size and power considerations

2.13.

We estimated power based on means, standard deviations, and within-patient scale correlations over 6 months derived from our recent RCTs conducted with >500 patients as well as from the recent literature [37,38,46,53,61]. We originally planned to enroll 530 participants to randomize 400. However, due to a lower observed than estimated randomization rate in enrollment after study initiation (45.7%), we increased the target enrollment. We now estimate we will need to enroll ~875 patients to sufficiently safeguard against dropout before baseline and low post-discharge HADS scores at baseline to randomize 400. We conservatively assume 19% cumulative post-randomization dropout by 1 month, leaving 324, as well as an additional 15% dropout between 3 and 6 months [37,38,46]. Assuming a baseline standard deviation of 8.7 and correlation between baseline and 1 month of 0.4, this sample size will provide 90% power with an alpha of 0.05 to detect a treatment group difference of 2.6 units in the 3 month HADS total score, which represents an enduring effect difference similar to the minimal clinically important difference [62–64] in a comparison of two means via repeated-measures analysis. This will also provide 99% power with an alpha of 0.05 to detect a 2-unit difference in the primary outcome, the HADS total score at 1 month, as well as a 3.8-unit difference in the PTSS secondary outcome [61,65]. For subgroup analyses, in a comparison of two means in a repeated-measures analysis between baseline and 3 months, assuming a standard deviation of 4.5 and correlation between baseline and 3 months of 0.5, we will have 80% power with an alpha of 0.02 (to reasonably account for multiple comparisons) to detect group differences in the HADS total score of 4.2 units with a subgroup n of 100, 5.6 units with an n of 80, and 6.0 units with an n of 60, effects similar to those seen in the Blueprint 1 pilot RCT [38]. Power calculations were conducted via the comparison of two means in a repeated measures design in PASS (NCSS, Kaysville, UT).

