One potential limitation of our intervention is that the app platform might be challenging for participants who struggle with mobile phone navigation. We have attempted to address these issues by assisting patients with app set-up before discharge and by sending them home with a postcard containing contact numbers for support. A known limitation of our study is that it does not estimate the intervention's effects in the sickest of ICU patients due to the challenges in retaining participants with ongoing severe health challenges, which may limit the generalizability of these findings to more severely ill ICU patients. To improve generalizability of findings, we have adapted the intervention to Spanish-language speakers and have selected sites to maximize geographic and demographic diversity. However, though we can assess generalizability through subgroup analyses, app usage and intervention effectiveness may differ in a real world setting including broader populations and without CRC set-up assistance and follow-up. We have used a three-step iterative approach to translate the Blueprint intervention to Spanish with the goal of making the translation easily understandable and culturally relevant to a Latin American Spanish-speaking population, but it is possible we may not have adequately captured culturally relevant clinical and psychological concepts given the heterogeneity of Hispanic and/or Latinx populations.

Our work to date has been focused on identifying a patient-friendly and cost-efficient intervention that addresses the psychological sequalae of having survived an ICU admission for cardiorespiratory distress. With this large-scale multi-site RCT, we will investigate whether these differences are clinically and statistically significant among a large and diverse group of individuals, with respect to race, ethnicity, geography, and language, and determine whether these results are consistent across subgroups. We will also conduct exploratory analyses identifying patient-level characteristics, clinical factors (such as illness severity) or other social drivers of health associated with a greater treatment response. Identifying these factors will enable us to continue to fine-tune our approach in preparation for scaling the intervention to a population level, making it a ubiquitous resource for patients and their families during their transition after ICU discharge.

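### The plan promises to judge whether the effect is consistent across subgroups, but fits separate subset models and specifies no estimate or test of a difference in effect

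*Protocol article*

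**What the plan says.** The Statistical analysis section of the Protocol article states the subgroup question and the method in one sentence: "utilizing cLDA models as described above on subsets of participants, we will examine whether the intervention effects are consistent or vary in magnitude". The subgroups are "Black race, Hispanic ethnicity, and participants with Spanish as a primary language". The model it refers back to has a shared baseline intercept, changes from baseline, and treatment differences at the follow-up times, adjusted for site and language. Estimates carry 95% CIs, and p-"values will be used to determine significant differences". The article specifies no treatment-by-subgroup term and no contrast between subgroups.

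Consistency is a prominent promise. The Abstract gives it as the purpose of the subgroup analyses, and the Discussion says the trial will "determine whether these results are consistent across subgroups".

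The Sample size section introduces the subgroup calculation with "For subgroup analyses, in a comparison of two means in a repeated-measures analysis between baseline and 3 months". Its inputs there are an SD of 4.5 and a baseline-to-follow-up correlation of 0.5. It claims "80% power with an alpha of 0.02 (to reasonably account for multiple comparisons") for treatment differences of 4.2, 5.6 and 6.0 units in subgroups of 100, 80 and 60. These are differences between arms within a subgroup, not differences in effect between subgroups.

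**The concern.** Whether an effect is consistent or varies is a question about a difference between two treatment effects. A model fitted only to Spanish-language participants estimates the effect in those participants. It gives no estimate, interval or test for how that effect differs from the effect in everyone else. The article lists only the three subsets and names no comparator subset, so even an informal side-by-side comparison is not set out.

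With no between-subgroup quantity defined, readers of the results are left to compare p-values, since p-values are the stated criterion for treatment differences. An effect that is significant overall but not in a small subset is not evidence that the effect is smaller there. At stake is what the trial can say about the groups it set out to include, which is a secondary aim. The primary comparison is not affected.

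**Working it through.** **1. Inputs** (Sample size section unless noted)
- Subgroup sizes 100, 80, 60; alpha 0.02 (two-sided assumed, as sidedness is not stated); power 80%; SD 4.5; correlation 0.5; stated detectable differences 4.2, 5.6, 6.0.
- Whole trial: SD 8.7; correlation 0.4; 2.6 units at 3 months; 324 of 400 remaining at 1 month.
- 1:1 allocation (Experimental condition allocation).

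All calculations use the normal approximation and treat the subgroup size as the number analysed.

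**2. Reproducing the stated subgroup figures**

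Detectable difference = (2.326 + 0.842) × s × √(4/n), with s = SD × √(1 − r²) for a baseline-adjusted comparison. For SD 4.5 and r = 0.5, s = 3.90.

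| n | s = 3.90 | s = 4.5 (no baseline adjustment) | Stated |
|---|---|---|---|
| 100 | 2.5 | 2.9 | 4.2 |
| 80 | 2.8 | 3.2 | 5.6 |
| 60 | 3.2 | 3.7 | 6.0 |

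The stated values are not reproduced. They also do not scale with 1/√n: 4.2 at n = 100 implies 4.2 × √(100/80) = 4.7 and 4.2 × √(100/60) = 5.4. The SD of 4.5 also conflicts with the 8.7 used for the same scale. So no single set of subgroup inputs can be relied on, and a range is shown below.

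**3. Power within a subgroup if the effect is a uniform 2.6 units, alpha 0.02**

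Power = Φ(2.6/SE − 2.326), plus a negligible opposite tail.
- (a) SE implied by the stated detectable differences: 4.2/3.168 = 1.33, 5.6/3.168 = 1.77, 6.0/3.168 = 1.89.
- (b) SD 8.7 with r = 0.5 (the whole-trial SD with the subgroup correlation): s = 8.7 × √0.75 = 7.53; SE = 7.53 × √(4/n) = 1.51, 1.68, 1.95.
- (c) SD 4.5, r = 0.5: SE = 3.90 × √(4/n) = 0.78, 0.87, 1.01.

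| n | (a) | (b) | (c) |
|---|---|---|---|
| 100 | 36% | 27% | 84% |
| 80 | 20% | 22% | 74% |
| 60 | 17% | 16% | 60% |

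Under (a) and (b) a perfectly consistent effect would miss significance in most subgroup analyses. Under (c) it would usually reach it.

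**4. How often a uniform effect gives a discordant pattern**

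The probability that the rest of the sample is significant and the subgroup is not is (power in the rest) × (1 − power in the subgroup). With 400 analysed, a 2.6-unit effect, SD 8.7, r = 0.4 and alpha 0.05:
- n = 60: 0.852 × (1 − 0.243) = 65%
- n = 100: 0.806 × (1 − 0.371) = 51%

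With SD 4.5 the figures are 27% (n = 60: 1.000 × (1 − 0.734)) and 8% (n = 100: 1.000 × (1 − 0.916)). An interaction test at alpha 0.05 would wrongly indicate a difference 5% of the time.

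**5. What a direct contrast could detect**

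SE of the difference in effects = s × √(4/n + 4/(N − n)); detectable difference at 80% power and alpha 0.05 = 2.802 × SE. With SD 8.7 and N = 324:

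| n | r = 0.4 (s = 7.97) | r = 0.5 (s = 7.53) |
|---|---|---|
| 100 | SE 1.92; 5.4 units | SE 1.81; 5.1 units |
| 80 | SE 2.05; 5.8 units | SE 1.94; 5.4 units |
| 60 | SE 2.28; 6.4 units | SE 2.16; 6.0 units |

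With N = 400 the range is 4.9 to 6.3 units.

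**The case against.** The article does not say that a non-significant subset result will be read as no effect or as inconsistency. It promises estimates with 95% CIs, and its sentence on p-values concerns treatment differences within the models. Comparing estimates and intervals across subsets is an equally natural reading. This stands: a reader might infer that the plan will declare the app ineffective in a subgroup on a p-value alone, but the text does not support that.

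A reader might also infer that a consistent effect would usually look absent in these subgroups. That depends on the SD. It follows from the article's detectable differences or from SD 8.7, but not from its stated SD of 4.5. That SD is weak evidence because it contradicts the rest of the section, yet it is the stated input and has to be shown.

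Nor does the low power come from fitting separate models. It comes from small subgroups, and subgroup contrasts from a joint model would have nearly the same standard errors. The interaction is itself imprecise: under SD 8.7 it detects only differences about twice the 2.6-unit target or more. This also stands. What a joint model gains is an answer to the stated question, not more power.

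Finally, the second study aim, to "determine which patient-level characteristics are associated with a greater treatment response among sociodemographic subgroups of interest", is only weak support here, because the Discussion assigns that kind of question to separate exploratory analyses. The case rests on the Abstract, the Statistical analysis section and the Discussion.

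None of this supplies the missing contrast. The article names the method, so this is not a detail left to an unseen analysis plan.

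**Conclusion.** The concern holds as a mismatch between question and method. The article says it will determine whether effects are consistent across subgroups, and the analysis it specifies never estimates or tests a difference in effect. This follows from the text and needs no numerical assumption.

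The numbers show only that within-subset significance would be an unreliable stand-in. Under a uniform 2.6-unit effect, subgroup power ranges from about 16% to 84%, depending on which of the article's conflicting inputs is used. This assumes two-sided testing, a normal approximation, and subgroups of 60 to 100, which are the article's power scenarios and not recruitment forecasts. The 2.6 units are the 3-month target. For the 2-unit difference that the article uses at 1 month, power would be lower on the same inputs, and dropout within the subgroup would lower it further.

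This should be corrected. It bears on a secondary aim and leaves the primary result untouched.

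**What to change.** Replace the subset models with one constrained longitudinal model on all randomised participants, including treatment-by-time-by-subgroup terms, one factor at a time: Black versus not, Hispanic versus not, Spanish versus English app. Then:
- Report the difference in treatment effect with its 95% CI as the main output, with the interaction p-value alongside.
- Keep the within-subgroup estimates as descriptive.
- State that non-significance in a subgroup is not evidence of no effect, and that non-significance of the interaction is not evidence of consistency.
- State the sensitivity of the interaction with its assumptions: with SD 8.7 and correlation 0.4 to 0.5, about 5 to 6.4 units at 80% power and alpha 0.05 for subgroups of 100 down to 60.
- Reconcile the subgroup SD of 4.5 with the 8.7 used for the same scale and with the stated 4.2, 5.6 and 6.0 units.

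The cost is wording in the protocol and analysis plan; no new data are needed. Recruitment is planned to run to October 2027 and the statisticians are masked until final analysis, so the change can still be pre-specified. The downside is that the wide interval for the difference becomes visible.
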